## Abstract

Risk communication has been found to be a driver of nocebo effects in medical settings by enhancing negative expectations. In fact, merely disclosing the risk of side effects and complications of treatments or medical procedures increases reports of adverse events. Along these lines, it has been proposed that the occurrence of headache after lumbar puncture (LP), a routine diagnostic procedure in neurology, is caused to a large degree by the information delivered by the physician during the informed consent procedure. As withholding information conflicts with principles of patient autonomy, strategies are needed to mitigate nocebo-associated headaches without omitting the disclosure of risks. Here, we present a detailed study protocol for a preregistered, prospective, double-blind, randomized controlled clinical trial with N = 80 inpatients at the neurology department of the University Hospital Essen who have an indication for a diagnostic LP. The trial is designed to test whether optimized communication strategies aimed at minimizing nocebo effects during the informed consent procedure reduce headache-related impairment after LP compared to standard-of-care. Secondary outcomes include expectation of side effects, state anxiety, headache intensity and duration, use of on-demand pain medication, perceived warmth and competence of the physician, and satisfaction with the procedure.

## Introduction

1

The nocebo effect refers to adverse outcomes that arise due to negative expectations. Classically, such effects are evident in adverse events reported in placebo arms of randomized controlled trials (RCTs), where adverse events in the placebo arm are often of similar quality and quantity to those in the verum arm, meaning that a large proportion of side effects are actually attributable to non-drug-related effects. For example, the nocebo effect was recently demonstrated in a systematic review and meta-analysis of large phase-III trials of COVID-19 vaccines (Haas et al., 2022a), in which 76% of reported systemic side effects were found to be unrelated to the actual receipt of the vaccine (Haas et al., 2022a). Subjective symptoms are particularly susceptible to the effects of negative expectations (Liccardi et al., 2004; Wolters et al., 2019). Headache, for instance, is one of the most commonly reported side effects in placebo arms of RCTs (Howick et al., 2018; Duncan et al., 2024). Nocebo-related headaches have also been observed following media coverage about health risks, with increased rates of headache after news reports about side effects from vaccinations against COVID-19 and human papillomavirus (HPV) as well after the reformulation of a thyroxine medication (Faasse et al., 2012, 2017; [name] et al., 2024). Moreover, nocebo-related headaches have also been confirmed in studies employing controlled test environments (Stovner et al., 2008; Benedetti et al., 2014). There is extensive empirical evidence demonstrating the powerful impact of the nocebo effect on health and wellbeing. Recent research has focused on both internal and external factors that contribute to the nocebo effect and has examined its neurobiological and neurochemical underpinnings (for recent reviews, see Colloca, 2024; Grosso et al., 2024).

The nocebo effect is well documented in placebo-controlled clinical trials and experimental work, but its relevance for clinical reality extends far beyond the application of inert treatments (Planes et al., 2016). For example, a study in healthy participants found that the analgesic effect of the highly potent opioid drug remifentanil on experimentally induced pain was almost entirely nullified when participants were told that the infusion of remifentanil had been stopped, despite the fact that it actually continued unchanged (Bingel et al., 2011). Such findings highlight the power of verbal suggestion as a potent driver of nocebo effects, in addition to prior negative experiences (Zunhammer et al., 2017). Communication by healthcare providers frequently conveys unintentional negative suggestions, increasing anxiety and arousal and facilitating the generation of nocebo effects in medical care (Lang et al., 2005; Vranceanu et al., 2012; Greville-Harris and Dieppe, 2015; Stortenbeker et al., 2018; Borelli et al., 2021). Critically, the mere act of informing a patient about risks and side effects of a provided treatment or procedure can itself increase the likelihood of a patient experiencing them. For instance, in a study on sexual dysfunction during finasteride treatment, 43.6% of the men who were informed about the rare occurrence of erectile dysfunction, decreased libido, and ejaculatory disorders reported experiencing these side effects, compared to only 15.3% of the patients who were not given this information (Mondaini et al., 2007).

Especially, when an invasive diagnostic procedure is planned, patients are routinely informed about relevant risks and potential complications before giving consent. The lumbar puncture (LP) is a particularly common diagnostic procedure in neurology, used to collect cerebrospinal fluid (CSF) from the spinal canal. Investigation of CSF is part of the basic workup of a plethora of neurological and neuropsychiatric symptoms and is often critical for the diagnosis of inflammatory processes of the nervous system (e.g., meningitis, encephalitis, multiple sclerosis, inflammatory neuropathies), subarachnoid hemorrhage, neurodegenerative diseases (e.g., Alzheimer’s disease), or oncological processes (e.g., meningeal carcinomatosis) (Jane and Wray, 2024). It involves inserting a needle into the subarachnoid space of the spinal canal at the lumbar level to passively drain CSF. A known potential side effect of this procedure is postdural puncture headache (PDPH) (Plewa and McAllister, 2024), which is thought to be caused by intracranial hypotension, resulting in strain on the meninges. Symptoms typically appear within 48–72 h and are usually, though not exclusively, orthostatic, that is, worsening when upright and improving when lying down (Plewa and McAllister, 2024). The incidence reported in the literature varies widely, ranging between 2 and 40%, but generally not exceeding 10% when atraumatic needles are used (Nath et al., 2018; Tumani et al., 2019; Plewa and McAllister, 2024). Given that lumbar puncture is a routine procedure, with thousands performed worldwide every day, any reduction of the burden of headaches due to nocebo effects is, therefore, likely to be impactful.

Back in 1981, Daniels and Sallie suggested that a significant proportion of headaches following lumbar puncture may be less related to the pathophysiology of PDPH and more likely to be nocebo-mediated, non-specific headaches (Daniels and Sallie, 1981). In their study of 28 patients, the risk of headache was disclosed to 15 patients but not to the remaining 13 patients. Upon assessing headache incidence at 4- and 24-h post-LP, seven (47%) of the informed participants reported headache, compared to only one person (8%) in the uninformed group. The results of this single study, with a small sample size and an ethically questionable approach, need to be interpreted with caution. However, given the known susceptibility of headaches to nocebo effects as well as the role of risk disclosure in promoting side effects, the potential for significant nocebo effects remains plausible. Importantly, this presents an ethical dilemma in medical practice: On one hand, informed consent is essential for preserving patient autonomy and must be upheld to ensure transparently informed consent and health-related decision-making. On the other hand, physicians are obligated to avoid potential harm from nocebo effects, in line with the principle of *primum non nocere*—first, do no harm.

A potential solution to this dilemma lies in the use of communication strategies that reduce negative expectations and minimize nocebo effects without obscuring risks or deceiving patients (Bingel and Placebo Competence, 2014). Several strategies targeting verbal and non-verbal communication have been successfully tested in experimental studies. *Positive attribute framing* of a risk entails stating the probability of *not* experiencing a side effect (Faasse et al., 2019). For example, this was demonstrated in a study on cybersickness in virtual reality, which found that participants who were told that “7 out of 10 people will not experience nausea” reported less nausea than participants who were told that “3 out of 10 people will experience nausea” and participants who were given general information about nausea occurrence (Mao et al., 2021). *Positive message framing* can be used to reframe the experience of a side effect as something positive and has been found, for example, to increase vaccine acceptance and reduce nocebo effects after vaccination against SARS-CoV2 (Bender et al., 2023; Crum et al., 2023). The use of *positive wording* and the avoidance of anxiety-laden terms can reduce perceived pain from needle injections (Varelmann et al., 2010). Furthermore, as discussions are frequently dominated by the possibility of adverse events, even if such events are uncommon, *emphasizing the value and goal* of a medical procedure helps to bring about a balanced risk–benefit assessment. Naming treatment benefits alongside risks has been shown to reduce nocebo weakness after insertion of a pain catheter (Zech et al., 2022). Moreover, goal setting is known to positively influence treatment adherence (Coppack et al., 2012) and health outcomes (Rief et al., 2017), while lack of clarity in treatment goals can lead to a less effective treatment (Geurtzen et al., 2020). *High warmth and empathy of the healthcare professional, conveyed through verbal and non-verbal cues,* lead to fewer reported side effects (Barnes et al., 2024), and warmth and competence positively influence outcome expectations (Seewald and Rief, 2024). One strategy to achieve positive doctor–patient communication is to *validate* patients’ experiences, which has been shown to be effective in attenuating nocebo effects (Greville-Harris and Dieppe, 2015). Finally, providing educational *information about the nocebo effect* resulted in reduced negative treatment expectations and fewer reported side effects (Pan et al., 2019; Michnevich et al., 2022; Gorner et al., 2024).

There are further promising strategies to attenuate the nocebo effect that have not yet been directly tested but have been shown to boost placebo effects or positively influence factors that, in turn, modulate nocebo effects (Bingel and Placebo Competence, 2014). For instance, research on attention and learning shows that information that is delivered first (*primacy effect*) and last (*recency effect*) is more easily retained in memory. Therefore, opening and closing an informed consent procedure (ICP) with positive aspects helps the patient to keep these aspects in mind for later consideration. Narrating from a *patient-centered perspective* rather than a doctor-centered perspective during medical consultation for a placebo with an alleged concentration-enhancing effect was found to lead to a higher intention to take the placebo (Haas et al., 2022b). Moreover, explicitly *addressing patients’ needs and specific concerns* during the consultation was shown to positively change patients’ attitudes toward participating in mammography screening (Fissler et al., 2015). Finally, *pointing out measures taken to prevent unwanted effects* can convey safety and competence, while *outlining effective coping strategies* that the patient can utilize in the case of adverse events empowers self-efficacy and reduces fear.

The goal of this study is to implement a protocol that encompasses optimized communication strategies to assess their effect on patient-reported headache-related impairment and overall burden after diagnostic lumbar puncture. Specifically, the study aims to test whether such communication can reduce nocebo-related symptoms without compromising the relevant content for informed consent. The publication of the detailed study protocol serves to improve reproducibility and transparency and to facilitate the translation of these strategies for use in clinical practice.

## Methods and analysis

2

### Trial design

2.1

This prospective study was conducted using a parallel-group design with two groups. In the experimental group, the optimized communication protocol was applied (OPT), whereas the standard-of-care group (SOC) received communication according to a control protocol that uses standard communication observed in the clinic with no particular consideration of the effects of communication. The required sample size for the planned analysis of the main outcome (i.e., complete datasets from t1 to t5) was N = 80 inpatients, recruited in the general wards of the Neurology Department at the University Hospital Essen, with a balanced 1:1 group allocation ratio (n = 40 for SOC, n = 40 for OPT). The study was preregistered at the German Clinical Trials Register (DRKS00032272). This study protocol aligns with the SPIRIT guidelines (Standard Protocol Items: Recommendations for Interventional Trials) and follows the SPIRIT-PRO extension for patient-reported outcomes, as specified in Supplementary Table S1 (Chan et al., 2013; Calvert et al., 2018).

### Ethics statement

2.2

The study protocol was approved by the Ethics Committee of the University Hospital Essen (22-11020-BO) on June 14, 2023.

### Inclusion criteria

2.3

Any adult (minimum 18 years old) with a medical indication for an elective, that is, planned lumbar puncture for diagnostic purposes during an inpatient stay on a general ward in the Neurology Department at the University Hospital Essen. The indication as well as the absence of contraindications for LP were confirmed by the ward physicians and by the study physician.

### Exclusion criteria

2.4

Patients were not eligible if one or more of the following criteria were met: presence of contraindications against LP, as defined in guidelines (Engelborghs et al., 2017; Tumani et al., 2019), which include elevated intracranial pressure, infection at the puncture site, use of anticoagulant medications, coagulopathy, or thrombocytopenia; emergency indication for lumbar puncture; insufficient mental capacity to provide informed consent; impaired consciousness; limited ability to complete surveys on an electronic tablet; intended therapeutic purpose of lumbar puncture (i.e., spinal tap for suspected intracranial idiopathic hypertension or normal pressure hydrocephalus); history of prior lumbar puncture (or failed attempts); extreme scoliosis, extreme obesity with BMI > 50, or other medical conditions likely to complicate lumbar puncture; indication for performing lumbar puncture under fluoroscopy; presence of a chronic headache condition according to the International Classification of Headache Disorders (ICHD)-3 criteria and/or 15 or more headache days in the last 30 days; headache as the primary complaint leading to admission or LP indication.

### Criteria for discontinuing study participation

2.5

Study participation was to be terminated preemptively if the following occurred after enrollment: LP no longer indicated by medical personnel or the patient declined or aborted the procedure; failed attempt at lumbar puncture with no collection of CSF; patient retroactively withdrew consent for study participation or for use of the data; other medical or logistical barriers to study continuation on the part of the patient (e.g., discharge before the LP, significant deterioration in health, extended unavailability or incompliance of the patient for study participation) or the study personnel (e.g., unplanned unavailability of study personnel without adequate replacement or feasibility of rescheduling the lumbar puncture); later emergence of exclusion criteria (i.e., change in LP indication to a therapeutic CSF drainage). Patients who did not complete study time point t5 (3 days after LP) for any of these reasons will not be included in the final per-protocol analyses.

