#### Lumbar puncture (LP)

2.12.4

The patient was approached in his/her hospital room for the LP. Once the patient had adopted the required position and the physician had thoroughly disinfected the skin area, prepared a sterile field, and was just putting on sterile gloves, the patient was asked to rate how nervous he/she currently felt about the imminent LP on an NRS from 0 (not at all) to 10 (worst imaginable nervousness). Upon successful puncture (indicated by CSF backflow), the patient was asked to rate the pain during needle insertion from 0 (no pain at all) to 10 (worst imaginable pain). After completion of the procedure, the physician left the room and immediately noted the number of necessary needle insertions into the skin until successful CSF drainage, the size and length of the needle used, and the total number of milliliters of CSF collected. The total contact time between physician and patient (from the physician entering to leaving the room) was noted.

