#### Survey time point 6 (t6)—3 months after LP

2.12.8

A final online survey and telephone interview were conducted 3 months (target: 12 weeks = 84 days) after LP as a follow-up. The online survey assessed generic symptoms in the past 7 days and their attribution to the LP (modified GASE), the overall satisfaction with the LP, current headache intensity, headache-related impairment since LP, and minimum, maximum, and mean headache intensity. Participants’ beliefs about their study group allocation and the study’s overall goal were also queried. In the telephone interview, patients’ knowledge of their diagnosis and their illness perception were assessed again (modified B-IPQ). Finally, patients were asked whether they had a known diagnosis of primary headache and whether the number of days with headache and of days requiring pain medication due to headache per month had changed between the 3 months before and the 3 months after LP. Specifically, the occurrence of a new headache that persisted and never faded for at least 15 days since LP was queried. Headache characteristics were assessed again to determine their alignment with a specific headache disorder.

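### A failed or aborted puncture ends study participation, not only the procedure, so the comparison is conditioned on post-allocation events and no later headache ratings are planned for these patients

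*Protocol article*

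**What the plan says.** Section 2.5 of the protocol article opens its list with "Study participation was to be terminated preemptively if the following occurred after enrollment". The events are of different kinds:

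- Puncture not done or not finished: "LP no longer indicated by medical personnel or the patient declined or aborted the procedure", and "failed attempt at lumbar puncture with no collection of CSF".
- Consent: "patient retroactively withdrew consent for study participation or for use of the data".
- Barriers, given by example: "other medical or logistical barriers to study continuation on the part of the patient (e.g., discharge before the LP, significant deterioration in health", followed by a prolonged period in which the patient cannot be reached, non-compliance, and staffing problems.

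The consequence for the analysis follows: "Patients who did not complete study time point t5 (3 days after LP) for any of these reasons will not be included". Section 2.14.1 confirms that the analysis is per protocol. Section 2.7 places allocation after enrolment and ends recruitment in each group when 40 is reached without counting dropouts. It also states that the physician who gives the talk and does the puncture is the one person who knows the allocation.

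On puncture difficulty, Section 2.12.4 records "the number of necessary needle insertions into the skin until successful CSF drainage", while Table 2 lists an attempt count without that condition. At three months, Section 2.12.8 states that "the occurrence of a new headache that persisted and never faded for at least 15 days since LP was queried".

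**The concern.** Only withdrawal of consent obliges the trial to stop asking questions. A patient whose puncture fails has had the whole allocated talk and at least one needle attempt. On the trial's own hypothesis, that headache after the procedure is driven largely by what the patient was told, this patient can have the primary outcome. Yet no t3 to t6 survey is planned.

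The removal criterion may also depend on arm. The Discussion counts turning down or breaking off needed investigations among the consequences of nocebo effects, which is what the intervention is meant to reduce. The decision that an attempt has failed rests with an unblinded physician. If failure or abortion differs by arm, a comparison of 40 replaced completers per arm no longer compares the groups as randomised. For patients removed before t3, a different analysis set cannot help, because no post-puncture rating was taken.

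**Working it through.** **1. The plan's own figure.** Section 2.7 gives power 0.90 for f = 0.16 with 80 patients. For the group-by-time interaction with 2 groups, 3 time points and alpha 0.05, assuming a correlation of 0.5 and sphericity (neither is stated), the noncentrality is 0.16² × 80 × 3 / (1 − 0.5) = 12.3. With 2 and 156 degrees of freedom the power is 0.885. The f that gives exactly 0.90 is 0.164, which rounds to the stated 0.16. The figure is reproduced, and nothing in this point changes it. It describes 80 completers, so the lost patients lie outside it.

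**2. How many are lost.** Inputs from Section 2.7 are 80 analysed patients and 15% attrition.

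- Enrolled: 80 / (1 − 0.15) = 94.1, so 94 to 95.
- Lost: 94 − 80 = 14, or 95 − 80 = 15.

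**3. What each kind of event loses.**

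| Event in Section 2.5 | Needle insertion? | What is lost |
|---|---|---|
| No longer indicated, declined, discharged before LP | No | No post-puncture headache data |
| Aborted | Possibly | If a needle was inserted, all later ratings |
| Failed, no CSF | Yes | t3 to t6 |
| Deterioration or long unavailability | Not stated | Ratings after the event; completed t3 and t4 exist but are left out of the per-protocol analysis |
| Consent withdrawn | Either | Collection properly ends |

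**4. What the loss could do.** Let k be the lost patients who had a needle insertion. Let D be the amount, in NRS points, by which their between-arm difference departs from that of the 80 completers. If they split evenly between arms, the difference over all patients with an insertion shifts by k / (80 + k) × D. The article gives neither k nor D. The values below are assumptions: 5 and 7 are about a third and a half of the losses, and 15 is a ceiling.

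| k | k / (80 + k) | D = 1 | D = 2 | D = 3 |
|---|---|---|---|---|
| 5 | 5/85 = 0.059 | 0.06 | 0.12 | 0.18 |
| 7 | 7/87 = 0.080 | 0.08 | 0.16 | 0.24 |
| 15 | 15/95 = 0.158 | 0.16 | 0.32 | 0.47 |

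If k is 0, the shift is 0.

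**The case against.** The strongest reply is that the number affected is probably small. Section 2.4 excludes conditions likely to complicate the puncture, and Section 2.8 describes one operator with about 100 previous punctures. The outcome is worded and timed from the lumbar puncture, and the Introduction attributes postdural puncture headache to low intracranial pressure. Restricting the outcome to completed punctures is therefore defensible for that headache type. It is less so for the nocebo headache that the trial targets. The article also condenses a fuller protocol, so its silence on retention procedures is weak evidence. But the termination rule and the exclusion are stated, not merely left unsaid.

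A reader might infer more than the text supports:

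- *That nothing is collected from anyone who stops.* The t1 and t2 surveys precede the puncture, and t3 and t4 precede t5. Ratings given before the event exist, and the article does not say that they are discarded.
- *That the patients at highest risk are lost.* No headache risk is given for failed punctures or deteriorating patients.
- *That deterioration after the puncture, or one missed survey, ends participation.* Deterioration is an example of a barrier and is not placed after the puncture. The availability criterion concerns a prolonged absence.
- *That attempts are recorded only in successful punctures.* Section 2.12.4 reads so, but Table 2 does not. The point is unclear.
- *That a large share of headache cases vanishes.* With an assumed incidence of 20 to 25%, 80 completers have 16 to 20 cases. Even if all of an assumed 5 to 7 lost patients had headache, they would be 5/25 = 20% to 7/23 = 30% of all cases. Every input to that share is assumed, so it is no estimate.

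**Conclusion.** The point holds in a limited form. The protocol ends participation, and with it survey follow-up, after a failed puncture or an aborted procedure. It then excludes and replaces these patients. That conditions the comparison on post-randomisation events which communication may influence, and an unblinded physician judges some of them. It is a weakness of design and reporting; no sample-size figure is wrong because of it.

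The only documented scale is 14 to 15 anticipated losses of all kinds. Whether bias is nil or reaches a few tenths of an NRS point depends on how many losses follow a needle insertion and how they differ by arm, and the article gives neither. Arm-dependent loss is plausible from the Discussion but is not shown.

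**What to change.** **Rule, for the protocol as a model for later studies.** Split Section 2.5 into events that end the procedure and events that end survey follow-up. Consenting randomised patients with at least one needle insertion, successful or not, keep the t3 to t6 surveys, timed from the last insertion. Withdrawal of consent still ends collection. State that the attempt count is also recorded for failed punctures, and align Sections 2.9 and 2.12.4 with Table 2. This concerns surveys only; when to abandon a puncture is not at issue.

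**This cohort.** Recruitment was set for December 2023 to May 2024, so surveys never given cannot be added. Report the number of terminations by reason and arm, and whether each came before the talk, after the talk, or after a needle insertion. Add a sensitivity analysis of all randomised patients who have any post-puncture rating and whose consent to data use stands. It should use a repeated-measures model that accepts incomplete series, so that t3 and t4 ratings from patients without t5 count. It will not recover failed punctures that were never surveyed, and the report should say so. Any t6 rating of impairment since the puncture is supportive only, because a three-month recall is not interchangeable with the interval ratings.

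**Cost.** For this cohort, one table and one extra model. For a later study, a wording change and a few more contacts through the existing online surveys and telephone calls, some with patients who may be unwell.
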